### Instruments

At the beginning of the trial, a joint evaluation by study staff and the ward team will be carried out for each of the 12 recommendations on a scale from 0 (= not implemented at all) to 9 (= fully implemented). This weighting is realized by with a Likert scale with typical anchor examples for each recommendation for the scores 0, 3, 6, and 9.

For the recording of violent incidents, the guidelines recommend the use of the SOAS-R (28). This instrument is most widespread throughout Europe and has already been introduced at many clinics in Germany. It is a well validated instrument with a score ranging from 0 to 22 (higher ratings stand for more severe incidents). In order to compensate problems of under- and over-reporting as much as possible, events will be considered only above a minimum score of 10 points. This allows both individual events and their severity to be taken into account. Furthermore, SOAS-R outcomes can be treated as continuous variables also. However, some of the participating hospitals will have introduced other, possibly less standardized instruments in their clinical practice. To avoid unwanted effects of increasing awareness in the course of the introduction of a new instrument, these hospitals will be advised to continue with their introduced instrument without any change in the practice of application.

### Sample Size

The primary outcome (number of coercive measures per bed and year) will be compared in a matched pair design, using a special stratification for matching of wards. Since the magnitude of the effect is not known for formal sample size estimation, the case count estimation is based on a realistic estimation of feasibility. The realistic number of wards participating in a nationwide study is assumed to be about 50. Using a paired two-sided t-test, using the primary outcome as continuous variable and the significance level of 5% and a power > 80%, an effect size of 0.6 can be detected with this case number (nQuery 8.1 Professional, exactly: 24 pairs = 48 wards). From a clinical point of view, an even larger effect is expected from the implementation of clinical practice guidelines. Since data is probably not normally distributed, however, the Wilcoxon test for paired data should be used as an evaluation method. This requires about 5%–10% more observations (or rather pairs) to compensate for the loss of power. Accordingly, a case number of 26 pairs (=52 wards) was specified. Drop-outs are not to be assumed in this trial, since the relevant outcome data must be collected from each ward for purposes of routine reporting anyway.

### Randomization

The wards will be randomized to intervention group or waiting-list control group by a 1:1 randomization. The participating wards will be matched in pairs following the best-fit principle according to the two criteria baseline frequency of coercive measures and initial value of the Likert scale for conformity with the implementation goals. Because this is a crucial confounder, the randomization will be done stratified accordingly. To get a matched-pair design to control at most for this confounder, the wards will be ranked by this variable (see “instruments”). In each of pairs in this ranked list a block randomization with a block size of two will be done by the randomization-software ROM in the independent Institute of Epidemiology and Med. Biometry, Ulm University. The matched wards must not belong to the same hospital in order to avoid spill-over effects.

### Data Collection

The documentation and reporting of coercive measures is legally stipulated in the federal State of Baden-Württemberg in a standardized form with a manual containing definitions of different coercive measures in the mental health law. All hospitals must record raw data in this regard and transmit it to the federal state-wide register. Standardized forms for electronic data entry are already available and there is a well-established practice in this regard. The possibility of an evaluation for individual clinical units and time periods is therefore possible without large additional expenditure. The raw data stored in the electronic medical records will be used. Data will be fully anonymized and it will no longer be possible to assign information to individual patients, even for clinical staff. The possibility of cumulative, care unit-related evaluation is a prerequisite for participation in the study. The raw data is stored in the respective clinics together with the corresponding medical records for the legally required retention period. For the study purpose, no raw data is transferred to the evaluation center, but only cumulative evaluations according to the described outcomes. Participating hospitals will be provided with tables to fill in for this purpose. Because no patient-related data is collected, no anonymization or pseudonymization is required. The cumulative data is stored at the evaluation site in connection with the relevant ward. A special concept for the purposes of data protection was established according to the requirements of the funding agency.

### Statistical Analysis

The main outcome number of coercive measures per bed and year is evaluated by comparing the ward pairs by the paired Wilcoxon test at the significance level of 5%. Secondary outcome is also evaluated by the paired Wilcoxon test. In order to control confounding and reduce bias, the analyses are supplemented by multiple regression models (linear mixed models and/or generalized conditional logistic regression models) including possible covariates (number of admissions, average occupancy, proportion of involuntarily treated patients, average staffing levels). These analyses will be interpreted explorative. Raters will not be blinded due to the fact that control and interventions wards will be analyzed at different time points and additional analysis (pre-post comparison) are needed for the control wards.

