## Methods

### Study Design

This multicentre study applies a mixed-methods design. In this interventional trial, wards are randomized in a 1:1 ratio to either an intervention or a control condition (waiting list), stratified by the amount of coercive measures per bed and month/year and the implemented aspects of the guidelines to matched pairs. In addition, a waiting-list control design allows for a pre-post analysis for participating wards of the waiting list group. Furthermore, this design allows for analyzing if observer effects already lead to a reduction of coercive measures between the baseline and the start of the intervention as well as for assessing potential spill-over effects in the control group during the waiting time. After 12 months, control wards will receive the intervention. Pre-post analysis will also be done or interventions wards which provide additional data of one year of follow-up after the intervention. Moreover, a complementary qualitative trial in form of interviews with participating staff will be performed.

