### Standard of Care on Control Wards

The legal requirements (mental health laws, civil code) already require the use of coercion to be limited to a necessary minimum. The participating wards should continue to apply their current strategies to prevent coercion and violence, even if they are randomized into the control group and even if these strategies are also mentioned in the 12 interventions. New structured programs especially with external supervision to reduce coercion and violence further should not be implemented in this phase. However, control wards will be informed about the program and its possibilities and spill-over effects cannot be ruled out. To detect such effects, a second measurement of implementation status and outcomes will take place on the control wards before the beginning of the intervention after the waiting list status.

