### Outcomes

The primary endpoint will be the number of coercive measures per bed and month/year for each ward (intervention wards vs. waiting list wards). This dependent variable includes forced medication, physical and mechanical restraint as well as seclusion. We chose this primary outcome according to its frequent use in the international literature in studies on ward level: 61 out of 78 studies on the topic reduction of coercive measure chose this endpoint (7). By the calculation per bed ward of different sizes become comparable. We are using aggregated information derived from routine data of the wards. No personal data is collected.

Secondary outcome will be cumulative duration of freedom-restrictive measures (seclusion, restraint) per bed and year (in hours) as well as the change before and after the intervention for each ward of the waiting list group (waiting list period vs. intervention period).

Important variables to be controlled for will be

status of implementation at the first visit (measured with a Likert scale, see next par).number of aggressive incidents per bed and year (measurement see next par).staffing levelspercentage of involuntary admissions

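### The reasons given for not blinding do not apply to the randomised year-1 comparison, whose central analysis could be run on coded arms

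*Protocol article*

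**What the plan says.** The blinding decision is one sentence in the Statistical Analysis section of the protocol article: "Raters will not be blinded due to the fact that control and interventions wards will be analyzed at different time points". The sentence goes on to a second reason, that "additional analysis (pre-post comparison) are needed for the control wards".

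Other sections bear on whether these reasons hold:

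- **Primary contrast (Outcomes):** "number of coercive measures per bed and month/year for each ward (intervention wards vs. waiting list wards"), a comparison between arms.
- **Crossover (Study Design):** "After 12 months, control wards will receive the intervention".
- **Waiting-period measurement (Standard of Care on Control Wards):** "a second measurement of implementation status and outcomes will take place on the control wards before the beginning of the intervention".
- **Pre-post contrast (Outcomes):** listed as a secondary outcome, "the change before and after the intervention for each ward of the waiting list group (waiting list period vs. intervention period").
- **Data flow (Data Collection):** hospitals fill in tables, and the evaluation centre receives "only cumulative evaluations according to the described outcomes", stored with a link to the ward.
- **Allocation (Randomization):** generated by an independent university institute.
- **Supporting models (Statistical Analysis):** "linear mixed models and/or generalized conditional logistic regression models", with possible covariates, to be read as exploratory.

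**The concern.** The article does not merely leave blinding unmentioned. It takes a decision and justifies it, and the justification does not support the decision for the analysis that matters most. A later within-ward comparison in the waiting-list group needs the labels when it is run, but it does not require them to be known while the randomised comparison is being done.

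Staff on an intervention ward necessarily know what they are doing, so the central analysis is one of the few places where masking remains possible. Some discretion is left at that stage: how implausible ward totals are queried, whether the rate is taken per month or per year (Outcomes allows both, while Statistical Analysis says year), and which model and covariates support the main result. If these are settled with the arms known, the result is open to a criticism that a simple coding step would answer.

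**Working it through.** **1. The plan's own figures, and whether blinding touches them.** Inputs from Sample Size: paired two-sided t-test, alpha 5%, power above 80%, effect size 0.6, 24 pairs, raised by 5% to 10% for the Wilcoxon test to 26 pairs. Power comes from the noncentral t distribution with n − 1 degrees of freedom and noncentrality 0.6 × √n.

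- 23 pairs give 78.5% and 24 pairs give 80.4%, so 24 is the smallest number above 80%.
- 24 × 1.05 = 25.2 and 24 × 1.10 = 26.4, so 26 lies in the stated range.
- Simulated Wilcoxon power at 26 pairs (5,000 runs, normal pair differences, effect 0.6) is about 82%.

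The sample size reproduces. Blinding enters none of these formulas.

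**2. The timing reason.** Control wards cross over after 12 months, and their outcomes are measured before they do. If the intervention and waiting periods run side by side, the data for the randomised contrast are complete before any control ward starts its intervention phase. The timeline figure is not shown, so this concurrency is read from Study Design and Standard of Care on Control Wards. The different time points then arise only from the later phase. Taken literally, the phrase would mean that the two arms' outcomes for the primary contrast are analysed at different times. That would conflict with a concurrent paired comparison. On either reading the sentence has to be reconciled with the other sections.

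**3. The pre-post reason.** The pre-post change is a separate secondary outcome within the waiting-list group. It can be run after the labels are released.

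**4. Whether coded analysis is feasible.** The primary test needs pair membership and two labels, not their meaning. In a test case with 26 pairs, the two-sided paired Wilcoxon p-value was 0.00241 with the labels one way and 0.00241 with them swapped. The evaluation centre receives only cumulative tables, and a body independent of the wards already holds the allocation. Because the tables are stored with the ward's identity, the wards would need codes.

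**5. What central masking cannot reach.** As an illustration, assume no true effect and a systematic difference in recording between arms, expressed in SDs of the pair difference (26 pairs, normal differences, 5,000 runs). These shifts are assumptions; the article gives no such figure.

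| Assumed recording shift (SD) | Rejection rate |
|---|---|
| 0 | 4.7% |
| 0.1 | 7.4% |
| 0.2 | 16.5% |
| 0.3 | 30.9% |

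A shift of this kind arises on the wards, and masking the analyst would leave it unchanged. The table shows the limit of the remedy, not the size of the bias it would prevent.

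**The case against.** The strongest reply is that the sentence concerns raters, not analysts. The rating the article describes is the implementation score, agreed jointly by study staff and the ward team and measured again on control wards after the waiting period. Those people cannot be masked. This stands: a reader might infer from the sentence's place under Statistical Analysis that the analyst knows the arms, but the article does not say so.

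A reader might also infer that the team delivering the intervention cleans the totals and chooses the models. No section says who staffs the evaluation centre, and such detail is commonly left to the full protocol or analysis plan.

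It is tempting, too, to measure the problem by counting the regression specifications left open. That count describes how open the models are, which masking does not change, and it concerns analyses the article itself calls exploratory.

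Finally, masking is not free. A query on an implausible total has to go back to an identified ward that knows its arm, so someone must stand between ward and analyst. The outcome is also routine data collected anyway, which limits central discretion. All of this reduces the benefit. It does not repair the stated reasons, which still fail to cover the randomised comparison.

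**Conclusion.** The point holds in a limited form. The grounds given for not blinding do not apply to the randomised year-1 comparison, which is complete before the control wards cross over and is separate from their pre-post analysis. This rests on the intervention and waiting periods running concurrently.

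The gain from masking the central analysis is modest. It protects data handling and the choice of supporting models; the confirmatory test is already fixed. The size of any bias from unmasked handling cannot be derived from the article. Sample size, alpha and power stay as they are. This is a low-cost improvement in wording and procedure, not a flaw that threatens the primary result.

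**What to change.** Replace the blinding sentence in Statistical Analysis with text to this effect:

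- Ward staff, visiting research workers and those who rate implementation jointly cannot be blinded.
- The analyst receives the year-1 ward tables with coded wards, pairs retained and arms labelled A and B.
- The paired Wilcoxon tests for number and for duration, and the choice of supporting model and covariates, are closed on the coded data. Queries to wards go through the existing study-centre contacts.
- The labels are released afterwards, and the pre-post analyses follow.

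The same edit should define who the raters are and remove or explain the phrase about different time points.

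The cost is a small coding step, the routing of queries through someone other than the analyst, and a short delay before the pre-post analyses can begin. No new data are needed.

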### Qualitative Analysis

For the qualitative evaluation, researchers will interview one or two selected key persons at each of the participating wards during the course of the implementation. It is planned that one researcher at each study center will be responsible for the implementation and for identifying the key persons. The key persons will be interviewed *via* telephone by another researcher. An interview guide will be prepared for this purpose. The interviews will be recorded, transcribed and subjected to a qualitative content analysis according to Mayring (29) using the MAXQDA program. Different categories will be developed to identify typical barriers and favorable factors for a successful and sustainable implementation. This content analysis technique is broadly applied in social sciences to evaluate large quantities of material from semi-structured interviews. It allows to build categories of content and to count certain text components (e.g., aspects of stigmatization, safety feeling and ward atmosphere).

## Discussion

The outlined trial will be a nationwide mixed-method study on the implementation of evidence- and consensus-based guidelines on reduction of coercion in mental health care. To our knowledge, there were only smaller studies on guideline implementation in psychiatry in general with inconsistent results so far (30). With regard to a related topic of the objective addressed here, the process of involuntary hospital admission in the USA was improved by implementing guidelines (31). In Germany, complex guidelines on handling psychotropic medication during agitation could be implemented in a cluster-randomized design in nine nursing homes in Berlin and were compared with nine control facilities; significant improvements on the level of patient-related outcomes were observed (32). In 15 registered psychiatrist offices in Munich, a computer-assisted decision aid for therapy decisions based on schizophrenia guidelines was implemented, which at least initially showed improvements over a control group (33). Another relatively small study in Germany referred to the implementation of the medication in schizophrenia guidelines on four wards, with relative improvements in a pre-post design (34).

With the potential to promote relevant changes in mental health care, this study is intended to realize the transfer of expert knowledge as well as the results from clinical trials into clinical routine. The main risks for successful guideline implementation lie in the current scarcity of human resources in hospitals. The study only makes experts or consultants available to the wards, but not additional nursing or therapeutic personnel. It is well-known that the implementation of measures to reduce violence and coercion can be time-consuming and personnel-intensive. Additionally, large studies harbour the risk that implementation varies considerably in quality and extent across participating centres, resulting in the worst case scenario of zero effects on average, as it happened in a study on joint crisis plans (35, 36). This risk is to be countered by recording the score of the Likert scale developed especially for this purpose.

## Ethics Statement

The studies involving human participants were reviewed and approved by The project was approved by the Ethics Committee of the University of Ulm on September 4th, 2019, No. 55/19. Written informed consent for participation was not required for this study in accordance with the national legislation and the institutional requirements.

